## Abbreviations

|               |                                          |
|---------------|------------------------------------------|
| ACE    | Angiotensin converting enzyme            |
| AE     | Adverse events                           |
| ANCOVA | Analysis of covariance                   |
| ASA    | Acetylsalicylic acid                     |
| ATC    | Anatomical therapeutic classification    |
| CABG   | Coronary artery bypass grafting          |
| CAT    | COPD assessment test                     |
| CHF    | Chronic heart failure                    |
| CI     | Confidence interval                      |
| COPD   | Chronic obstructive pulmonary disease    |
| CRF    | Case report form                         |
| CRT    | Cardiac resynchronisation therapy        |
| GSE    | General self-efficacy scale              |
| HADS   | Hospital anxiety and depression scale    |
| HR     | Hazard ratio                             |
| ICD    | International classification of diseases |
| KM     | Kaplan Meier                             |
| MID    | Minimal important difference             |
| mMRC   | Modified Medical research council        |
| PCC    | Person-centred care                      |
| PT     | Preferred term                           |
| SAP    | Statistical analysis plan                |
| SD     | Standard deviation                       |
| SOB-HF | Shortness of breath in heart failure     |
| SOC    | System organ class                       |

## 1 Background

The aim of this project is to evaluate if person-centered care (PCC) in the form of a combined eHealth and structured telephone support available at home will improve general self-efficacy and reduce self-reported sick leave for patients with chronic pain.

This statistical analysis plan (SAP) is describing the study's quantitative objectives and planned analyses for the study's main manuscript. The qualitative part, other quantitative sub-studies, and health economic evaluations will be planned in a separate document.

## 2 Study Objectives and Hypothesis

### 2.1 Primary Objective and Hypothesis

Does a person-centred intervention via a combined telephone and e-health support for people with chronic pain, in comparison with a control group, lead to:

- increased self-efficacy?
- reduced rate of self-reported sick leave?

The hypothesis is that PCC increases self-efficacy and reduces rate of self-reported sick leave.

## 3 Study Design

### 3.1 Treatment Groups/Exposure

The treatment groups will be called as following:

- Intervention
- Control

## 4 Study Populations

### 4.1 Full Analysis Set/Intention-to-Treat Population

All randomized patients will be included in the Intention-to-Treat (ITT) population.

All ITT summaries will be performed on as-randomized groups.

## 5 Study Variables

### 5.1 Baseline/Patient Characteristics Variables

Baseline is defined at the date of randomisation and counted as day 1 in study.

#### 5.1.1 Demographics and Baseline Characteristics

Following demographics and baseline characteristics will be described:

- Age (years)
- Sex (Male, Female)
- Diagnosis (M25, M54, M79, R52)
- Living situation (Married/living together, Living apart, Single)
- Education (Compulsory school or lower, Upper secondary or high school, Post-secondary vocational school, College/University)
- Country of birth (Sweden, Other)

- Pre-specified medical history
  - Depression (F32)
  - Anxiety (F41)
  - Exhaustion disorder /stress (F43)
  - Insomnia (G43)
  - Migraine (G43)
  - Hyperactivity disorder (F90)

## 5.2 Concomitant Medications

Use of following pre-specified medications will be described:

- Opioids (N02A)
- Antidepressants (N06A)
- NSAID/ Coxibes (M01AB, M01AE, M01AH, M02AA)
- Gabapentinoids (N03AX)
- Capsaicine (N01BX04)
- Carbamazepin (N03AF01)
- Sedatives (N05A/B, R06AD1/2, R06AD52)
- Muscle relaxants (M03BB03, M03BC, M03BX01)
- Sleep medication (N05C)
- Other analgetics, antipyretics, anesthetics (N02BA01, N02BA51, N02BE01, N01BB02)
- Other (C02AC01)

## 5.3 Efficacy/Outcome Variables

### 5.3.1 Primary Variable

In line with previous RCTs evaluating PCC the primary outcome will be a composite comprised of general self-efficacy and self-reported sick leave after 6 months. Each participant will be classified as improved, deteriorated, or unchanged at six months as follows:

- Improved is a participant who has a reduced degree of self-reported sick leave and an increased self-efficacy by  $\geq 5$  units, which is seen as a clinically relevant improvement.
- Deteriorated is a participant who has an increased degree of self-reported sick leave or a decrease in self-efficacy by  $\geq 5$  units.
- The participants who are neither improved nor impaired are counted as unchanged.

In case of missing data the last available data will be carried forward if available, otherwise unchanged value will be imputed that is corresponding to baseline data carried forward.

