## 6 Statistical Methods

### 6.1 Sample Size

To achieve 80% power based on a p-value of 0.05 (two-tailed) for an increase in the proportion of improved patients from 20 to 40% in the primary outcome a sample size of 91 patients in each group was required. However, the study team planned to include 110 patients in each group to account for withdrawals/dropouts. Thus, a minimum of 220 patients were planned to be randomised across the two groups.

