### 6.4 Handling of Missing Data

Missing data will be handled as provided in the definition of the primary and secondary variables. See section 5.3.1 and 5.3.2. No other missing data will be imputed.

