### 7.3 Efficacy Analyses

#### 7.3.1 Primary Efficacy Analysis

The primary efficacy variable, the composite of change in the General Self-Efficacy (GSE) scale, degree of self-reported sick leave, evaluated at 6 months follow-up after baseline will be analysed as ordered categorical, with the categories: ‘Deteriorated’, ‘Unchanged’ and ‘Improved’. The primary variable will be analysed using Mantel-Haenszel chi-square trend test. The difference of proportions between the treatments for each category will be described along with the 95% CI for proportions.

A sensitivity analysis will be performed on the primary outcome without imputation.

Graphically, the categories of the primary variable will be presented using histograms.

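### Carrying values forward, with Unchanged as the fallback, is not a neutral rule for the trend test, and no planned analysis probes informative dropout

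*SAP*

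**What the plan says.** Section 5.3.1 defines the primary outcome as a three-level composite of self-efficacy (GSE) and self-reported sick leave at 6 months. On missing values it states: "In case of missing data the last available data will be carried forward if available, otherwise unchanged value will be imputed". It adds that the fallback amounts to carrying the baseline forward. A participant with a 3-month value therefore keeps the 3-month category, whichever it is, and a participant with no follow-up becomes Unchanged.

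Section 6.4 refers back to this rule ("Missing data will be handled as provided in the definition of the primary and secondary variables") and excludes any other imputation; section 6.2 says the same. Section 4.1 keeps all randomised patients in the analysis. Section 7.3.1 applies a Mantel-Haenszel trend test to the three ordered categories and names one check on missing data: "A sensitivity analysis will be performed on the primary outcome without imputation". Section 6.2 and Supplementary tables 2 and 3 in section 8 repeat that observed-data approach. The SAP states no missing-data assumption and has no multiple imputation or tipping-point analysis for the composite. The mixed model in section 6.2 covers continuous variables only.

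**The concern.** In a responder analysis, counting a missing participant as a non-responder is a penalty. In a trend test over three ordered categories, Unchanged is not a penalty, because it sits in the middle of the scale. Section 5.3.1 classes a participant as Deteriorated on either a rise in sick leave or a fall of at least 5 units in GSE, so real worsening among dropouts may be common, and the fallback erases it. If the arms lose different numbers or different kinds of participant, the rule moves their scores by different amounts.

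The confirmatory claim rests on one p-value (sections 6.2 and 6.3). Its only support against missing data is an analysis that leaves out the missing participants. That analysis can be biased in the same direction when dropout depends on outcome, so agreement between the two could be read as more reassuring than it is.

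**Working it through.** **Inputs from the SAP.** Section 6.1 powers the trial "for an increase in the proportion of improved patients from 20 to 40% in the primary outcome", states that "a sample size of 91 patients in each group was required", and says the team "planned to include 110 patients in each group to account for withdrawals/dropouts". Power is 80% and alpha is 0.05 two-sided.

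**Assumptions (not in the SAP).** The category mix, the dropout rate in each arm and how dropouts fare are all assumed. All scenarios below treat every dropout as having no follow-up data, which is the upper case for the fallback.

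**1. The plan's own figure.** Pooled-variance formula with mean proportion 0.30: n0 = [1.960·√(2·0.30·0.70) + 0.842·√(0.20·0.80 + 0.40·0.60)]² / 0.20² = 81.2, rounded up to 82. With continuity correction: n = (n0/4)·[1 + √(1 + 4/(n0·0.20))]² = 90.9, rounded up to 91. The stated figure reproduces. The implied loss is 1 − 91/110 = 17.3%, or 19 per arm.

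**2. Shrinkage of the estimate.** With random loss d, all coded Unchanged, the proportion Improved becomes p·(1 − d). At d = 17.3%: 0.20 × 0.827 = 16.5% and 0.40 × 0.827 = 33.1%. The gain is 20 × 0.827 = 16.5 points. For d from 10% to 30% the gain runs from 18.0 to 14.0 points.

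**3. The rule alone: random but unequal dropout, no true effect.** Score the categories −1, 0, 1. With 30/50/20% (Deteriorated/Unchanged/Improved) in both arms the true mean score is −0.10. Coding dropouts 0 multiplies it by (1 − d).
- Control, 10% dropout: −0.10 × 0.90 = −0.090.
- Intervention, 25% dropout: −0.10 × 0.75 = −0.075.
- Spurious difference: +0.015, favouring the intervention.
- Simulated trend test, 110 per arm: 3.6% false significance favouring the intervention, against 2.5%. Without imputation the difference is zero and the rate stays at about 2.5%.
- Mirrored mix, 20/50/30%: +0.10 × (0.75 − 0.90) = −0.015, against the intervention. The direction depends on the mix and on which arm loses more.

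**4. Unequal and informative dropout, no true effect.** Same 30/50/20% truth; dropouts are 50/40/10%. Observed share = truth − d × dropout share.

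| | Deteriorated | Unchanged (observed + missing) | Improved | Mean score |
|---|---|---|---|---|
| Control, 10% | 25.0% | 46.0 + 10.0 = 56.0% | 19.0% | −0.060 |
| Intervention, 25% | 17.5% | 40.0 + 25.0 = 65.0% | 17.5% | 0.000 |

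- With the rule: difference 0.060; false significance favouring the intervention about 10.6%.
- Without imputation: control −0.06/0.90 = −0.067, intervention 0/0.75 = 0, difference 0.067; rate about 9.4%.
- At 15%/20% dropout the rate with the rule is 4.2%.

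**5. Equal dropout.** With 17.3% in both arms and the same 50/40/10% dropouts in each, the rate is 2.5% in each direction.

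**The case against.** Much of the case for leaving the rule alone is sound, and it limits the point.

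- **The large inflation needs several conditions at once.** Dropout must be clearly unequal, dropouts must fare much worse, and none of them may have 3-month data. The SAP supports none of these. Its only implied figure, 17.3%, carries no difference between arms, and equal dropout of one kind gives no inflation.
- **The 3-month visit softens the fallback.** Only participants with no follow-up at all are set to Unchanged.
- **The shrinkage does not weaken the test relative to omitting the missing.** With random 17.3% loss in both arms, and assumed mixes of 30/50/20% control and 20/40/40% intervention, the trend test has about 79% power either way. A reader might infer from the 16.5 points that the rule costs the confirmatory test power; against the no-imputation analysis, these figures do not show it.
- **The sensitivity analysis is not empty.** Under random unequal dropout it removes the artefact in step 3. It misses informative dropout.
- **Multiple imputation is no cure for step 4.** That dropout depends on unobserved outcomes. Imputation within arm that assumes missing at random would give roughly the no-imputation difference (0.067), unless baseline and 3-month values predict the missing outcomes.
- **The rule is explicit and consistent**, and section 5.3.1 ties the composite to earlier trials of person-centred care.

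All of this stands. It does not make Unchanged a neutral or dependably conservative value, and it supplies no analysis that probes informative dropout.

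**Conclusion.** The point holds in a limited form. The rule can bias the primary test in either direction when dropout differs between arms: modestly if dropout is random (3.6% against 2.5% in the example), and more if it is also informative (about 10.6%). In the informative case the only sensitivity analysis is biased alike (about 9.4%). The estimated gain in Improved can shrink from 20 to 16.5 points, an upper case. All error rates rest on assumed mixes and dropout rates with no follow-up data.

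A reader might go further and conclude that the primary p-value is invalid as planned. The SAP does not support that: it gives no dropout rate by arm and no mechanism, and under equal dropout of the same kind the null error rate is nominal. This should be fixed, but it is not a fault that must be cured before the analysis can be used.

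**What to change.** In sections 5.3.1, 6.4 and 7.3.1:

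- Impute GSE and degree of sick leave by multiple imputation within randomised group, from baseline and 3-month values, age, sex and diagnosis. Derive the composite in each imputed data set, combine the results, and state how the trend-test result is combined (for example, by pooling the mean-score difference with Rubin's rules). Preferably make this the primary handling.
- Keep carry-forward and no imputation as sensitivity analyses.
- Add a tipping-point analysis that moves missing intervention participants step by step towards Deteriorated and reports where p reaches 0.05. This is the part that addresses dropout depending on unobserved outcomes.

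Section 6.2 and the table titles in section 8 would need matching edits. The cost is SAP wording and modest programming in the SAS 9.4 already named. The downside is less direct comparability with earlier trials that used carry-forward, which keeping that analysis largely preserves.

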### 5.3.2 Secondary Variables

Following secondary efficacy variables will be analysed:

- Composite comprised of general self-efficacy and self-reported sick leave (as 'Deteriorated', 'Unchanged' and 'Improved') after 3 months.
- Degree of sick leave at 3, 6 months. In case of missing data, the last available data will be used from baseline or post-baseline data collection:
  - Change in sick leave (as continuous variable)
  - Change in sick leave (as the categorical variable 'Deteriorated', 'Unchanged' and 'Improved')
- Change in GSE at 3, 6 months from baseline. In case of missing data, the last available data will be used from baseline or post-baseline data collection. GSE will be analysed through the following two variables:
  - Change in GSE (as continuous variable)
  - Change in GSE by  $\geq 5$  units (as the categorical variable 'Deteriorated', 'Unchanged' and 'Improved')

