### 6.2 General Methodology

The first analysis report will be performed using data up to 6 months that is the time point used in the primary analysis. Six months data will be analysed as main analyses and 3 months data as complementary.

Descriptively, continuous variables will be presented by mean, standard deviation (SD), median, minimum and maximum, and categorical variables by number and percentages.

For all efficacy analyses the relevant estimate will be presented for comparison between the groups, difference in means or/and proportions, accompanied by 95% confidence intervals (CI).

For test between the two groups with respect to dichotomous variables Fisher's exact test will be used, for ordered categorical variables Mantel-Haenszel chi-square test will be used, non-ordered categorical variables chi-square test will be used and for continuous variables T-test or Mann-Whitney U-test will be used.

The change in continuous variables over time will be evaluated by using mixed models for repeated measures using unstructured covariance matrix and adjusting for baseline value. Mean difference with 95% CI will be described along with p-values within and between treatment groups.

The primary analysis will be considered confirmed if the p-value  $< 0.05$  could be achieved. All other analyses will be considered as exploratory and the p-values will be interpreted as descriptive.

Figures of continuous variables over the follow-up period and change from baseline over the follow-up period will be given as box-plots and figures of dichotomous and ordered categorical variables over the follow-up period and change from baseline over the follow-up period will be given as vertical bar charts.

Missing data will be handled in the definition as primary and secondary variables. See section 5.3.1 and 5.3.2. No other missing data will be imputed.

Additional analyses will be performed using only non-imputed data.

All tests will be two-tailed and conducted at 0.05 significance level, following adjustments as described.

All analyses will be performed using SAS software version 9.4 (SAS Institute Inc. Cary, NC, USA).

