## 8 Planned Tables and Figures

| Table Number                  | Table Title                                                                                                                                                                                                            |
|-------------------------------|------------------------------------------------------------------------------------------------------------------------------------------------------------------------------------------------------------------------|
| Table 1.               | Demographics and baseline characteristics for intervention and control group. Data are presented as mean $\pm$ standard deviation, median (range) and number of observations, or number (percentage) (ITT population). |
| Table 2.               | Composite, self-reported sick leave and GSE at 3 and 6 months. Data imputed with Last Observation Carried Forward (LOCF) (ITT population).                                                                             |
| Table 3.               | Mean values self-reported sick leave and GSE. Data imputed with Last Observation Carried Forward (LOCF) (ITT population).                                                                                              |
| Supplementary table 1. | Pre-specified medical history and concomitant medication for intervention and control group.                                                                                                                           |
| Supplementary table 2. | Composite, self-reported sick leave and GSE at 3 and 6 months. No imputation of data (ITT population).                                                                                                                 |
| Supplementary table 3. | Mean values of self-reported sick leave and GSE. No imputation of data (ITT population).                                                                                                                               |

  

| Figure Number     | Figure Title                                                                                                                         |
|-------------------|--------------------------------------------------------------------------------------------------------------------------------------|

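### Continuous changes in GSE and sick leave are filled by carry-forward before a mixed model that needs no imputation, which pulls the main-table 6-month difference off target

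*SAP*

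**What the plan says.** SAP section 5.3.2 lists change in sick leave and change in GSE at 3 and 6 months as secondary variables, each in a continuous and a categorical form. For both outcomes it sets the same rule: "In case of missing data, the last available data will be used from baseline or post-baseline data collection". A participant with no follow-up therefore gets a change of 0 at both visits, and one seen only at 3 months has that value repeated at 6 months.

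Section 6.2 names the model: "The change in continuous variables over time will be evaluated by using mixed models for repeated measures using unstructured covariance matrix and adjusting for baseline". It also states what is reported: "Mean difference with 95% CI will be described along with p-values within and between treatment groups".

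Section 6.4 ties the two together: "Missing data will be handled as provided in the definition of the primary and secondary variables". Section 7.3.2 sends the secondary analyses to section 6.2 and adds no other rule. Section 8 titles main Table 3 "Mean values self-reported sick leave and GSE. Data imputed with Last Observation Carried Forward (LOCF) (ITT population"), and the non-imputed counterpart is Supplementary table 3. Section 6.2 also says: "Additional analyses will be performed using only non-imputed data".

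Sections 6.2 and 6.3 make everything except the primary analysis exploratory.

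**The concern.** A mixed model for repeated measures with unstructured covariance is usually chosen because it accepts incomplete records. A participant with a 3-month value and no 6-month value still informs the 6-month comparison through the estimated correlation, under missing at random. Once carry-forward has filled every gap, the model has nothing missing to handle and treats the repeated values as real 3- and 6-month measurements. Section 5.3.2 therefore removes the advantage of the model that section 6.2 selects.

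Self-efficacy and sick leave are the two questions in the study objective (section 2.1), and Table 3 is where their means appear in the main manuscript. What is at stake is whether the estimates and intervals printed there describe the 6-month difference, or a mixture of 6-month, 3-month and zero changes.

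**Working it through.** **The plan's own figure.** Section 6.1 gives 91 per group for 20% against 40%, 80% power, two-sided 0.05. The pooled formula gives (1.96·√(2·0.30·0.70) + 0.8416·√(0.16+0.24))² / 0.20² ≈ 81.2, so 82. The continuity correction gives (81.2/4)·(1 + √(1 + 4/(81.2·0.20)))² ≈ 90.9, so 91. The figure reproduces and is not in question. It is used here only for the dropout allowance: 1 − 91/110 = 17.3%.

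**Inputs.**
- From the SAP: 110 per group, visits at 3 and 6 months, and the carry-forward rule.
- Assumed: GSE SD 6, correlation 0.6 between visits, 9% with no follow-up and 8% with 3-month data only, and the trends and effects stated below.

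**Attenuation with equal dropout.** The expected carried-forward difference is (share with 6-month data × 6-month effect) + (share with 3-month data only × 3-month effect) + (share with no follow-up × 0). For a true 6-month difference of 3.0:

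| Assumed 3-month effect | Calculation | Estimate | Shrinkage |
|---|---|---|---|
| 3.0 | 0.83·3.0 + 0.08·3.0 | 2.73 | 9% |
| 2.0 | 0.83·3.0 + 0.08·2.0 | 2.65 | 12% |
| 1.5 | 0.83·3.0 + 0.08·1.5 | 2.61 | 13% |

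A simulation of 3,000 trials in SD units (effects 0.25 at 3 months and 0.50 at 6 months, 17.3% dropout split evenly around month 3) agrees. Carry-forward gave 0.437, where the formula gives 0.827·0.50 + 0.0865·0.25 = 0.435. The observed-data mixed model gave 0.502. Carried-forward data were analysed by baseline-adjusted ANCOVA at 6 months. On complete data this equals the unstructured mixed model if baseline-by-visit is included.

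**Standard errors.** In that simulation the carry-forward model SE was 0.105 against an empirical SD of 0.107, so it is right for its own estimator. The observed-data SE was 0.118. Multiplied by 6, these are 0.63 and 0.71; across the assumed scenarios the ranges are about 0.63 to 0.67 and 0.71 to 0.72. With no missing data at all, the SE would be 6·√(1 − 0.6²)·√(2/110) = 0.647. At the low end, carry-forward thus claims slightly more precision than complete follow-up would give.

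**Coverage.** With bias b and SE s, coverage of the true difference is Φ(1.96 − b/s) − Φ(−1.96 − b/s). For b = 0.27 and s = 0.63 this is 92.9%; for b = 0.39 it is 90.5%. The simulation gave 90.6% for carry-forward and 94.3% for the observed-data model.

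**Unequal dropout, no true effect.** Assume 10% dropout in control, 25% in intervention, and a 4-point improvement in both arms at 6 months. Each line is the intervention mean minus the control mean:
- half of dropout before month 3, full improvement by month 3: 4·0.875 − 4·0.95 = −0.30
- half before month 3, half the improvement by month 3: (4·0.75 + 2·0.125) − (4·0.90 + 2·0.05) = −0.45
- all dropout before month 3: 4·0.75 − 4·0.90 = −0.60

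Simulated rejection rates were 7.6% for the first pattern and 15.5% for the third. With a declining trend the sign reverses: in SD units, a trend of +0.5 gave −0.057 and a trend of −0.5 gave +0.055.

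**Where there is no bias.** With no true effect and equal dropout, simulated rejection stayed near 5% (4.6% to 4.9%). With unequal dropout and no trend it was also about 5%.

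**The case against.** Several points on the other side stand.

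- **Interval width.** A reader might infer that carry-forward gives a miscalibrated, too small standard error. It does not: the model SE matches the sampling SD of the carry-forward estimator. Undercoverage comes from the bias. The interval is too narrow only relative to the information observed.
- **False positives.** A reader might infer a general inflation of type I error. That needs unequal dropout and a common trend together, and the SAP gives neither. The 7.6% to 15.5% range illustrates an unfavourable case and is not a forecast.
- **Covariance.** Distortion of the 3- to 6-month covariance looks like a further fault. On filled data the model essentially reduces to the 6-month ANCOVA, and no harm from it was shown.
- **Competing test.** The t-test or Mann-Whitney option in section 6.2 could be read as a rival analysis of the same variables. It is a generic list by variable type, while the same section assigns change over time to the mixed model. It does not carry this point.
- **Existing safeguards.** The non-imputed analysis is already planned, the outcomes are exploratory, and the same carry-forward principle defines the primary composite (section 5.3.1), so there is a case for consistency.
- **Missing at random** cannot be tested, so the observed-data model is not simply the correct one. The size was worked out for a normally distributed GSE score; nothing comparable was shown for sick leave.

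These limit the point but do not remove it. Exploratory status relaxes error control without making an attenuated estimate suitable for the main table, and the SAP does not say which version prevails if the two differ.

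**Conclusion.** The point holds as an analysis choice worth changing. Read together, sections 5.3.2, 6.2, 6.4 and 8 run the mixed model on carried-forward values and place carried-forward results in main Table 3.

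Under the stated assumptions and equal dropout of about 17%, the cost is a 9 to 13% shrinkage of a 3.0-point GSE difference and coverage of about 90 to 93%. If dropout differs by arm and both arms change, the error can go either way, for example −0.3 to −0.6 points with 10% against 25% dropout and a 4-point common improvement. Carry-forward is therefore not reliably conservative. The mechanism applies to sick leave as well, but its size there is not established. The primary test and the sample size are not affected by this point.

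**What to change.** In sections 5.3.2 and 6.2, make the mixed model with arm, visit, arm-by-visit and baseline value, fitted to observed non-imputed data, the main analysis of continuous change in GSE and sick leave. Make Table 3 the non-imputed version and move the carry-forward version to Supplementary table 3 as a sensitivity analysis.

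The cost is SAP wording and a swap of two tables already planned; no new data are needed. The downside is explicit reliance on missing at random and somewhat wider confidence intervals (SE about 0.71 to 0.72 instead of 0.63 to 0.67 under the assumptions above).
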